## Hypothesis

The hypothesis to be tested is that long-term (more than 1 year's duration) bisphosphonate use for the treatment of post-menopausal osteoporosis or other benign bone disease is associated with impaired dental healing.

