#### Part 4: Medication history

A detailed description of oral glucocorticoids (start/stop dates, current dose and cumulative dose), hormone replacement therapy and other medications including raloxifene, calcitriol, tibolone, teriparatide and strontium will be recorded.

If a bisphosphonate has been prescribed, the type will be recorded including alendronate, risedronate, tiludronate, pamidronate, zoledronate or etidronate together with indication for use (osteoporosis, Paget's disease, glucorticoid-induced osteoporosis, metastatic disease, hypercalcemia). Doses of all bisphosphonates including start and stop dates and current doses will be recorded to allow calculation of cumulative drug doses.

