#### Power and sample size

The sample size estimate is based upon the assumption that the overall prevalence of bisphosphonate use in post-menopausal women is around 10%. Based on Australian Pharmaceutical Benefits Scheme (PBS) and Australian Bureau of Statistics (ABS) data the upper limit estimate is 19% [39]. Assuming that approximately 50% of these patients have used bisphosphonate for at least one year, then 10% prevalence of long-term use in this population appears to be a reasonable estimate. It is hypothesised that the prevalence of bisphosphonate use among those with delayed dental healing may be greater than 10%. A recent case series of patients with frank jaw necrosis found that all were treated with bisphosphonates [19]. We infer from this that the true proportion of women with DDH taking bisphosphonates may be greater than 30% - 50%. Given the expected low prevalence of DDH, the study plans to recruit 'controls' and 'cases' in a ratio of 4:1. An observed prevalence of greater than or equal to 30% bisphosphonate use amongst women with DDH would correspond to an odds ratio of around 3.85. Hence, for the purpose of this study, the minimum detectable difference will correspond to an OR greater than or equal to 3.85. This value is based upon a conservative estimate of the effect expected, rather than what is considered clinically important. The most relevant measure of clinical importance will be one derived from a cohort study, that is where the effect of bisphosphonate use can be represented in terms of a relative and/or absolute risk of delayed dental healing. Whilst ideal, this would require a very large sample and long-term follow-up.

A total sample of around 269 subjects (54 cases and 215 controls) will provide 90% power to detect a true OR of at least 3.85, given the expected prevalence of 10% bisphosphonate use amongst post-menopausal women in the community.

The relationship between bisphosphonate use and delayed dental healing will be assessed using a multivariate logistic model incorporating age, duration of exposure, relevant co morbidities, concurrent treatment, and other potential confounders as covariates.

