#### Potential covariates

Potential covariates include those data collected, which increase our knowledge of the potential to develop DDH. These include co-morbidities (medication history, smoking history, other medical conditions), oral hygiene habits and demographics (socioeconomic status, nationality).

Bisphosphonate use is considered an explanatory variable, which is also our exposure of interest.

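### The only stated model adjusts bisphosphonate use for duration of exposure, which is part of the exposure, so the use coefficient need not test the more-than-1-year hypothesis or have the stated 90% power

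*Protocol article*

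**What the plan says.** The Hypothesis section concerns "long-term (more than 1 year's duration) bisphosphonate use", and the Abstract and Conclusions repeat it.

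The last paragraph of Power and sample size gives the only inferential model. There, the association of the drug with delayed healing "will be assessed using a multivariate logistic model incorporating age, duration of exposure, relevant co morbidities". The same list goes on to name treatments given alongside and further confounders, and calls them all covariates.

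Potential covariates names the exposure without a threshold: "Bisphosphonate use is considered an explanatory variable, which is also our exposure of interest".

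Power and sample size is not uniform on what the 10% control prevalence measures. It first attaches about 10% to overall use. It then gives 19% as an upper limit and supposes a long-term share: "Assuming that approximately 50% of these patients have used bisphosphonate for at least one year". From this it draws its working figure: "then 10% prevalence of long-term use in this population appears to be a reasonable estimate". The final power statement refers to 10% bisphosphonate use, unqualified. That statement is 54 cases and 215 controls for 90% power at an odds ratio of 3.85, with 30% of cases exposed.

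Part 4: Medication history supplies what a duration analysis needs: "Doses of all bisphosphonates including start and stop dates and current doses will be recorded to allow calculation of cumulative drug doses".

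**The concern.** A confounder is a separate characteristic that can differ between exposed and unexposed people and also affects the outcome. Duration of bisphosphonate exposure has only one possible value, zero, in non-users. Adjusting use for duration therefore compares nobody like with like; it splits one exposure into two correlated terms.

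With both terms entered as written, the coefficient that a reader would take as the bisphosphonate effect answers a different question from the hypothesis. The sample size was built on a single binary exposure, so its power statement does not carry over to that coefficient. At stake is a null result for use when a real effect exists, in particular if risk grows with duration, a pattern the Background itself raises for osteonecrosis of the jaw.

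**Working it through.** **1. Reproduce the plan's figure.** Inputs from Power and sample size: 10% of controls and 30% of cases exposed, 4 controls per case, 90% power. Two-sided alpha of 0.05 is assumed, because the article does not state it.

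- Odds ratio: (0.30/0.70)/(0.10/0.90) = 3.857.
- Pooled proportion: (0.30 + 4 × 0.10)/5 = 0.14.
- Cases, uncorrected: [1.96 × √(1.25 × 0.14 × 0.86) + 1.2816 × √(0.30 × 0.70 + 0.10 × 0.90/4)]² / 0.20² = (0.7604 + 0.6180)²/0.04 = 47.5.
- With continuity correction: (47.49/4) × [1 + √(1 + 10/(47.49 × 4 × 0.20))]² = 53.56, so 54 cases; 4 × 53.56 = 214.2, so 215 controls; total 269.

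The plan's figure is reproduced. It is an unadjusted comparison of one binary exposure. Without the continuity correction, 54 and 215 give a power of Φ[(0.20 − 1.96 × 0.0528)/0.0656] = Φ(1.47) = 92.9%.

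**2. What the use coefficient means.** Write the model as logit P = α + βU + γD, with U = 1 for users and D = years of use, zero in non-users. The log odds ratio for a user of D years against a non-user is β + γD. So β alone is the contrast at D = 0. If D is centred at the users' mean m, the use coefficient becomes β + γm, the contrast at average duration.

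**3. Effect on power.** The article gives no duration distribution, so the distributions here are assumptions. Simulations used 54 cases and 215 controls (216 in the gamma row), a Wald test at two-sided 0.05, and linear uncentred duration.

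| Scenario | Power of use term, no duration | With duration |
|---|---|---|
| All users >1 year, uniform 1-10 years, constant OR 3.86 | 93% | 40% |
| All users >1 year, uniform 1-6 years, constant OR 3.86 | 93% | 34% |
| All users >1 year, 1 year plus a gamma variable (mean 3.5 years), constant OR 3.86 | 94% | 41% |
| All users >1 year, uniform durations, risk rising linearly | 93-94% | 3-5% |
| Any use, about half >1 year, effect only after 1 year | 73-75% | 9-16% |
| Any use, constant OR 3.86 at every duration | 94-95% | 72-76% |

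Hand check of the first two rows: the log odds ratio is ln 3.857 = 1.35 and its standard error without duration is about 0.38. Adding duration multiplies the standard error by 2.17 (1-10 years) or 2.43 (1-6 years). Then 1.35/(0.38 × 2.17) = 1.64 and Φ(1.64 − 1.96) = 37%; 1.35/(0.38 × 2.43) = 1.46 and Φ(1.46 − 1.96) = 31%. Both are close to the simulated values.

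In the rising-risk row the true β is zero by construction, so the use odds ratio centres near 1 (median 0.96) although users as a group have an odds ratio of about 3.86.

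**4. Choices that limit the loss.** With duration centred among users, power is 92-93% for long-term users with a constant effect, and 70-71% if any use is analysed with an effect only after 1 year. A joint 2-df test of use and duration has 74-99% across all scenarios.

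**5. If exposure were any use.** Take the 19% upper limit in controls, half of it long-term (9.5%) with odds ratio 3.857 and half short-term with odds ratio 1. The odds ratio for any use is (3.857 × 0.095 + 0.095)/0.19 = 2.43. Case prevalence is 2.43 × 0.19/(0.81 + 2.43 × 0.19) = 36.3%. Power is about 75% without and 70% with continuity correction, before any duration term is added.

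**The case against.** The strongest reply is that the size of the loss is not fixed by the text. The article does not say how use and duration are coded, whether duration is centred, or which test decides the hypothesis. A condensed article may leave such details to a full protocol or analysis plan, and some choices keep most of the power. It also does not call this model primary. All of that stands, and it makes the power figures conditional. It does not remove the fault in what is printed: duration is listed with the confounders, in the only model given.

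Three stronger readings are tempting, and the document does not support them.

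- **That most of the power is necessarily lost.** This holds under some codings and duration distributions and fails under others, as steps 3 and 4 show.
- **That use of 1 year or less is counted as exposed.** The sample-size text derives a long-term prevalence and then drops the qualifier, so bisphosphonate use may be shorthand for long-term use. The phrase in Potential covariates is a label and not a coding rule. The wording is ambiguous; the 2.43 dilution shows only what the looser reading would cost, using an upper-limit prevalence.
- **That use after the 2006 visit window will count as exposure.** The article states no cut-off date, but it does not say that later use counts, and an index date is a detail a fuller document could set. Visit dates, drug start and stop dates and, where recorded, precipitant dates are to be collected.

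**Conclusion.** The point holds in a conditional form. Listing duration among the confounders mis-specifies the model for the stated hypothesis, whatever the data turn out to be. With linear uncentred coding, the use coefficient is an extrapolation to zero years, and the stated 90% power does not apply to it.

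The numerical loss rests on assumed durations, the plan's 10% and 30% exposure, and two-sided 0.05. For long-term users, power falls from about 93% to about 34-41% with a constant effect, and to about 3-5% if risk rises with duration. It is smaller or absent under centring or a joint test, neither of which is specified. The shifting description of the exposure is a secondary fault of wording: the powered odds ratio of 3.85 should be tied to one defined exposure.

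**What to change.** State in Power and sample size and in Potential covariates that the exposure in the main model is more than 1 year of bisphosphonate use, and use that term consistently for the 10% and 30% prevalences. Remove duration of exposure from that model's covariates. Analyse duration and cumulative dose in a separate, secondary dose-response model, either in categories with non-users as reference or among users only.

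The cost is wording: start and stop dates and doses are already to be recorded. One small downside is that users of 1 year or less must be handled as a separate category, so that they are neither merged with long-term users nor silently placed among non-users.

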**Methods/Design:**

A case-control study has been chosen to test the hypothesis as the outcome event rate is likely to be very low. A total of 54 cases will be recruited into the study following review of all dental files from oral and maxillofacial surgeons and special needs dentists in Victoria where potential cases of delayed dental healing will be identified. Potential cases will be presented to an independent case adjudication panel to determine if they are definitive delayed dental healing cases. Two hundred and fifteen controls (1:4 cases:controls), matched for age and visit window period, will be selected from those who have attended local community based referring dental practices. The primary outcome will be the incidence of delayed dental healing that occurs either spontaneously or following dental treatment such as extractions, implant placement, or denture use.

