### Recruitment of Control Subjects

Each case will be matched with four controls randomly selected from those who have undergone dental treatment at the same dental practice from which the case originated. If access cannot be obtained to records from the originating dental practice, then a similar type of practice e.g. private practice or hospital - based practice, within a 10 km radius will be approached to provide control subjects. They will be matched for age (>50 years), gender and visit window period and will have no known defect in dental wound healing. If controls cannot be matched to the 6-month visit window period then they will be matched to within 12 months of the visit window period. Controls will be contacted by mail as for cases to obtain informed consent to study participation.

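### Controls are individually matched 1:4 on practice and gender, but the stated logistic model names neither these factors nor the matched sets, so the odds ratio may be pulled toward 1

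*Protocol article*

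**What the plan says.** The design is fixed in the section on recruiting controls, which states: "Each case will be matched with four controls randomly selected from those who have undergone dental treatment at the same dental practice". If that practice's records cannot be reached, a similar type of practice "within a 10 km radius will be approached to provide control subjects". The same section adds: "They will be matched for age (>50 years), gender and visit window period". The window may be widened to within 12 months.

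The abstract gives a shorter list. Its controls are "matched for age and visit window period, will be selected from those who have attended local community based referring dental practices", with no mention of gender, or of the practice being that of the individual case.

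The analysis is given in the last paragraph of Power and sample size. The association will be "assessed using a multivariate logistic model incorporating age". The other terms listed there are how long the exposure lasted, comorbid conditions, other treatments and an open-ended group of further confounders. Under Potential covariates, the demographic items named are socioeconomic status and nationality. Gender, practice and matched set appear in neither place.

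The planning inputs are 10% exposure ("given the expected prevalence of 10% bisphosphonate use amongst post-menopausal women in the community") and an effect stated as "30% bisphosphonate use amongst women with DDH would correspond to an odds ratio of around 3.85".

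**The concern.** Individual matching makes controls resemble their case on the matching factors. If those factors are related to exposure, controls also resemble cases on exposure more than a random control would. An analysis that pools all cases and all controls then gives an odds ratio nearer to 1 than the one that holds within sets.

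The condition is plausible here. The exposure is bisphosphonate use for post-menopausal osteoporosis or other benign bone disease, and the eligibility criteria do not exclude men, so exposure very probably differs by gender. It may also differ by practice, since the protocol itself distinguishes private from hospital-based practices. Age and window contribute little: nearly every eligible person (50 or over) meets the age criterion, and the six-month window is common to all apart from the fallback.

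This odds ratio is the study's only test of its hypothesis, so the model behind it should carry the design.

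**Working it through.** **1. The plan's own figures.** Inputs from Power and sample size: exposure 0.10 in controls and 0.30 in cases, ratio 1:4, 90% power. No alpha is stated; I assume two-sided 0.05.

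- OR = (0.30/0.70)/(0.10/0.90) = 3.857, against the stated 3.85.
- Pooled proportion = (0.30 + 4×0.10)/5 = 0.14.
- Cases for two independent groups: n = [1.96√(1.25×0.14×0.86) + 1.2816√(0.30×0.70 + 0.10×0.90/4)]² / 0.20² = (0.7604 + 0.6180)²/0.04 = 47.5.
- With continuity correction: (47.5/4)×[1 + √(1 + 2×5/(47.5×4×0.20))]² = 53.6, so 54 cases and 4×53.56 = 214.2, so 215 controls.

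The stated 54 + 215 = 269 is thus reproduced by the formula for two unmatched groups. The protocol states no within-set exposure correlation, which a matched formula would need.

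**2. Effect of ignoring the sets.** The documents give no between-set variation in exposure, so I assume a range. Let the logit of control exposure in a set be Normal(a, s²), with a chosen so that average control exposure is 10%, and let the within-set OR be 3.857. Then P0 = E[expit(a + sZ)] = 0.10, P1 = E[expit(a + sZ + ln 3.857)], and the pooled OR is [P1/(1−P1)]/[P0/(1−P0)].

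| Assumed SD s | P1 | Pooled OR | Shift toward 1 |
|---|---|---|---|
| 0 | 0.300 | 3.86 | 0% |
| 0.5 | 0.290 | 3.68 | 5% |
| 1.0 | 0.266 | 3.27 | 15% |
| 1.5 | 0.240 | 2.84 | 26% |

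For scale, the central 80% of sets would have control exposure of 5.0–16.1% at SD 0.5, 2.1–21.7% at SD 1.0 and 0.8–26.3% at SD 1.5.

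**3. Simulation.** 54 sets of 1:4, 4,000 studies per row, exposure as the only term, true OR 3.86.

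| SD | Median OR, pooled / conditional | Power, pooled / conditional | 95% CI coverage, pooled / conditional |
|---|---|---|---|
| 0 | 3.82 / 3.79 | 93.5% / 93.3% | 95.4% / 95.7% |
| 0.5 | 3.68 / 3.84 | 91.9% / 91.9% | 96.0% / 95.9% |
| 1.0 | 3.29 / 3.86 | 86.4% / 87.9% | 95.2% / 95.6% |
| 1.5 | 2.85 / 3.86 | 76.6% / 81.7% | 92.5% / 95.9% |

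With a true OR of 1 (20,000 studies per SD), the pooled median OR is 1.00 and the type I error is 3.3%, 3.2%, 2.5% and 1.9% at SD 0, 0.5, 1.0 and 1.5.

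**4. Gender alone.** Assume 40% men, with control exposure of 2% in men and 10% in women. Case exposure is then 3.857×0.02/(0.98 + 3.857×0.02) = 0.073 in men and 0.30 in women. P0 = 0.4×0.02 + 0.6×0.10 = 0.068 and P1 = 0.4×0.073 + 0.6×0.30 = 0.209. The pooled OR is (0.209/0.791)/(0.068/0.932) = 3.63, about 6% low. Stratifying on gender alone removed this in simulation (median 3.90).

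**5. Sets as indicator terms.** Entering 54 set indicators in an ordinary logistic model overshoots: the simulated median OR is about 6 for a true 3.86.

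**6. Matched sample size.** Dupont's formula for 1:4 matching, 90% power, OR 3.857 and 10% control exposure needs 45, 47, 49 and 55 cases for an assumed within-set exposure correlation of 0, 0.05, 0.1 and 0.2. With 54 cases the power is 94%, 93%, 93% and 90%.

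**The case against.** The strongest reply is that the protocol is silent rather than wrong. It never calls the model unconditional, conditional logistic regression is itself a multivariable logistic model, and a reference to other potential confounders leaves room for gender, which is recorded with the demographic data. An analysis plan that is not shown may settle this. That stands as a limit on the claim: the protocol cannot be said to have chosen an unmatched analysis. It does not remove the point, because the article states both the model and its covariates, these leave out the design, and the sample size is also that of an unmatched comparison.

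The matching is also loose. Only gender and, more weakly, practice can define the sets, and practice has a 10 km fallback. With matching this coarse, an unconditional model that includes the matching factors is a recognised alternative. That is accepted in the fix.

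A reader might infer three stronger things that the documents do not support:

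- That the odds ratio is certainly biased. It is not if practice and gender are unrelated to exposure or are adequately adjusted for, and every SD above is an assumption.
- That the interval and test would be invalid. Coverage stays near 95% up to SD 1.0, and under no association the test rejects too seldom, not too often.
- That entering age as a covariate is a fault because age is a matching factor. Matching only on being over 50 leaves age almost uncontrolled, so it belongs in the model.

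**Conclusion.** The point holds as a gap between design and analysis that should be closed before the data are analysed. Followed as written, the plan would understate the association wherever gender or practice predicts bisphosphonate use. The attenuation is about 5–15% for an assumed between-set SD of 0.5–1.0 and 26% at 1.5, which is an extreme assumption, and it is nil at SD 0. Power falls from 87.9% to 86.4% at SD 1.0 and from 81.7% to 76.6% at SD 1.5, relative to conditional analysis. The direction is well founded. The size depends on variation that the documents do not report. The sample size is sound on its own inputs and remains adequate for a matched analysis over the range of correlations examined.

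**What to change.** - Store an identifier for each matched set, and state that the primary analysis is conditional logistic regression on the sets. Keep age as a covariate and add a short, pre-specified list of confounders.
- Alternatively, justify an unconditional model that includes the matching factors (gender, practice type). Do not enter the sets as indicator terms.
- Reconcile the matching factors between the abstract (age and window) and Recruitment of Control Subjects (also gender and practice), so that it is clear what the analysis must condition on.

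The cost is a sentence or two and one stored variable. Sets in which all members have the same exposure carry no information in the conditional analysis, but the loss is negligible: 93.3% against 93.5% power when the sets are uninformative. No larger sample is needed, since 54 cases compare with about 45–55 under the matched formula for assumed within-set exposure correlations of 0–0.2.

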### Outcome measures

#### Primary outcome measures

The primary outcome will be the incidence of delayed dental healing that occurs either spontaneously or following dental treatment such as extractions, implant placement, or denture use.

#### Potential covariates

Potential covariates include those data collected, which increase our knowledge of the potential to develop DDH. These include co-morbidities (medication history, smoking history, other medical conditions), oral hygiene habits and demographics (socioeconomic status, nationality).

Bisphosphonate use is considered an explanatory variable, which is also our exposure of interest.

## Discussion

The present study seeks to determine the level of delayed dental healing that occurs either spontaneously or after dental procedures such as tooth extraction and how this relates to bisphosphonate usage. Delayed dental healing may be an earlier or less advanced lesion compared to ONJ but with a similar pathogenesis. By observing delayed dental healing as well as ONJ we may therefore more broadly describe bisphosphonate associated dental disorders and increase our power to find an association between bisphosphonate use and associated dental disorders. It is imperative to obtain a better understanding of this condition and its potential links to bisphosphonate use as it is often refractory to treatment and can lead to significant morbidity including bone sequestration, intraoral and extraoral fistula formation, secondary paraesthesia and pathological jaw fractures. The link between this and bisphosphonate use is paramount as there are a number of studies reporting the incidence of jaw osteonecrosis (a potential sequelae for delayed dental healing) to be as high as 0.09 - 0.34% in patients receiving oral and 6.7-9.1% in patients receiving intravenous bisphosphonates following dental procedures [40]. Furthermore, whilst the incidence of ONJ in osteoporosis patients in relation to bisphosphonate use has been reported to occur after prolonged treatment (greater than 3 years), it has been reported following 6-month use [41]. On the other hand, other data suggest an extremely low prevalence/incidence of ONJ in patients treated with bisphosphonates for osteoporosis and other metabolic bone disorders. Although an association between ONJ and bisphosphonate use has been suggested by case series, professional surveys and register data, there is a lack of controlled, population-based data. A key aim of the present study is to obtain such controlled data. By recording the prevalence of delayed dental healing and ONJ that occur in the absence of bisphosphonate use we hope to be able to estimate the true risk of these disorders in association with bisphosphonate exposure.

A case-controlled study design has been selected over a prospective cohort study. Whilst both are observational studies that could further knowledge of delayed dental healing, ONJ and bisphosphonate use, the former study design has a number of advantages. First, it will allow us to study an outcome with a potentially low incidence, less than 1% in patients with osteoporosis or Paget's disease [42]. Second, this approach will minimize the problem posed by a long latency between exposure to bisphosphonate therapy and the outcome of delayed healing and subsequent ONJ, something which cannot be accounted for easily in a prospective cohort study, except by extended follow-up. Third, we will be able to study the effects of other potential risk factors for delayed healing such as medical history including bisphosphonate usage, smoking history, dental hygiene, dental trauma including tooth extractions and implant placement, and denture usage on the outcome of interest, namely delayed dental healing. It is understood that a prospective cohort study would provide the most reliable assessment of the incidence of delayed healing, ONJ and bisphosphonates but to date such studies have not been conclusive [14].

One of the major limitations of this case-controlled study design is that it is reliant on information as it is recorded in the medical or dental history that may be incomplete and is subject to clinician bias and researcher interpretation. This is compounded by the fact that in 2006 there was considerable controversy regarding the role played by bisphosphonates in ONJ and the definition of the condition. Furthermore, resources required to access and collect data from thousands of medical and dental histories could result in a prolonged study period.

The present study also relies on recruitment of specialists to allow access to patient records followed by recruitment of cases and controls. All oral and maxillofacial specialists and special needs dentists in the state of Victoria will be invited to participate in the study but it will be difficult to control for ascertainment bias. Are practitioners who see delayed dental healing and ONJ more willing to allow review of their patient records? Are those who have a greater interest in the role played by bisphosphonates more likely to want to become involved? It is difficult to control for this even with the use of random sampling because practitioners' consent is required to allow file review. To some degree the same can also be said for patients with delayed dental healing. The patient information and consent brochure stipulates that this is an important study to further our understanding of the link between delayed dental healing and bisphosphonate use. Whether an individual who has taken a bisphosphonate may be more or less likely to participate is difficult to determine. Another potential limitation of the study is recollection bias given that some data will be collected via participant telephone interview. Furthermore, control subjects reading the patient information and consent brochure may feel that the study does not really benefit them and hence may be less likely to respond. The same can also be said for the general dental practitioners via whom the control subjects will be identified. If they have little experience with patients taking bisphosphonates or delayed dental healing, then they may have little motivation to allow a third party to access their patient records.

A key feature of the present study relates to the definition of DDH and ONJ. In 2005 the definition of osteonecrosis of the jaw was unclear and constantly changing in the literature and as such it was difficult to adhere to a single definition. The main disparity at the time was related to the length of time a wound took to heal before it fell into the category of osteonecrosis of the jaw. Initial healing, that is re-epithelialisation, of dental wounds such as those from dental extractions usually takes between 1 and 2 weeks [43]. Once the clot forms, fibrin and connective tissue begins to develop before the wound (in this case a dental socket) is closed over by epithelium. It then takes some weeks for the underlying socket to fill with bone and healing to be complete.

Hence up to 6 weeks for healing of a dental wound would be reasonable taking into account potential effects of delayed healing from medical co-morbidities such as steroid use or development and subsequent healing from complications such as a dry socket. Furthermore, in 2008, a report from the task force of the American Society for Bone and Mineral Research proposed that a "suspected" case of ONJ would be defined as "an area of exposed bone in the maxillofacial region that had been identified by a health care provider and have been present for less that 8 weeks" which was supported by others [42,44]. By this time, soft tissue closure and exposed bone would no longer be present. ONJ would then be the definitive diagnosis if greater than 8 weeks had lapsed for healing to occur [42,45,46]. The current definition for bisphosphonate associated ONJ includes the following features:

1. Current or previous treatment with a bisphosphonate

2. Exposed bone in the maxillofacial region that persisted for greater than 8 weeks and

3. No history of radiation therapy to the jaws [47].

An attempt also has been made to define clinical stages of ONJ [45,48] (AAOMS, 2007). Stage 1 involved the presence of exposed or necrotic bone that is asymptomatic with no evidence of infection. Stage 2 related to the presence of exposed necrotic bone and infection, erythema and the presence or absence of a purulent discharge. Finally stage 3, the most severe form of ONJ, contained all the characteristics of stage 2 but in addition, the presence of features such as a pathological fracture, draining sinus or communication either intra oral or extraoral and osteolysis. Since then, Stage 0 has been included to encompass patients with signs of ONJ but no exposed bone [46].

Potential covariates to be collected in this study are in line with those suggested as risk factors for ONJ and include dental factors such as tooth extraction, implant placement and denture use, treatment factors such as use of glucocortocoids and smoking status [26,29,49].

A critical component to the success or failure of any case-controlled study is recruitment of participants. The study was designed as a two-step recruitment process requiring not only patient participation but also clinician participation otherwise access to patient data and potential cases would have not been possible without employing more complex recruitment protocols. It is also imperative we seek the assistance of specialist practitioners in order to gain permission to screen consecutive patient records during the defined study time period in order to avoid selection bias associated with specialist recall of individual patient cases. Hence there are two potential problems with recruitment. The first lies with recruiting specialists. A number of key features have been identified to be essential to increase response rates in postal questionnaires [50]. A number of these features are also pertinent in the following study. Firstly, Edwards *et al.*, (2002) suggested that contacting participants before sending out questionnaires would be important. In the current study, the researchers presented the study outline and requirements of participants (clinician and patient) to oral and maxillofacial surgeons at a continuing professional development meeting. It is considered crucial to the study to recruit a high proportion of oral and maxillofacial surgeons as these are recognized as the group most likely to treat patients delayed dental healing following dental procedures. During this presentation the potential benefits of determining incidence of delayed dental healing with reference to bisphosphonate usage were discussed, which was considered to be of great interest to practicing specialists. This has also been determined as a potential method to increase response rate to postal surveys [50].

Other key factors employed to increase clinician recruitment included using personalized introductory letters, short questionnaires, follow-up letters to non-respondents and telephone follow-up. These are recognized strategies to increase recruitment [50]. Similar measures were also employed when recruiting potential cases and controls.

